#### Clinical protocol

First visit:
Parents/guardians are informed about the protocol of the study and the laser technique. They sign the informed consent form (see Supplementary data file S2 “Patient consent form”). Verbal assent from the child is obtained.The teeth are cleaned and polished with a rubber cup and pumice paste.A visual inspection of the vestibular surfaces of the investigated teeth and SoproLife® Daylight and SoproLife® Blue fluorescence digital images are made and recorded.Application of fluoride varnish Clinpro™ White Varnish 5% Sodium Fluoride over the whole vestibular surfaces of all anterior maxillary teethThe chosen method, CO_2_-laser irradiation or placebo, is applied.Follows direct adhesive bonding of orthodontic brackets

Second visit:
The teeth are cleaned and polished with a rubber cup and pumice paste.The incidence, extent, and severity of the lesions are assessed using ICDAS criteria and SoproLife® daylight and blue fluorescence. The data are recorded and digital photographs are made.Reapplication of the fluoride varnish Clinpro™ White Varnish 5% Sodium Fluoride

Third visit:
The teeth are cleaned and polished with a rubber cup and pumice paste.The incidence, extent, and severity of the lesions are assessed using ICDAS criteria and SoproLife® daylight and blue fluorescence. The data are recorded and digital photographs are made.Reapplication of the fluoride varnish Clinpro™ White Varnish 5% Sodium Fluoride

#### Criteria for discontinuing or modifying allocated interventions

The patient withdraws consentInter-current illness preventing further treatment

### Outcomes

#### Primary outcome measures

The primary outcome measures are the number of newly appeared caries lesions and the changes into ICDAS scores in the experimental and control teeth (within one patient) from baseline to 12 months. The International Caries and Detection System (ICDAS) is a visual scoring system developed for use in clinical assessment and clinical research of caries development and progression. It uses a numbered scoring system with a range from 0 to 6, to grade enamel demineralization and cavitation. Code of “0” represents unaffected/sound enamel, no caries change; “1” first visual change represents initial demineralization that is visible only after air drying; “2” represents a distinct visual change in the enamel that is visible when the surface is wet; “3” represents localized enamel loss or breakdown, no visible dentin or underlying shadow; and “4-6” represent larger carious lesions in dentin. Time frame: 1 year.

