**Methods and analysis:**

This is a protocol for a randomized, split-mouth controlled, clinical trial. The participants will be children aged 12–18 years at high caries risk, requiring fixed orthodontic treatment. The vestibular surfaces of maxillary anterior teeth of eligible patients will be exposed to CO_2_-laser irradiation in combination with fluoride therapy and fluoride therapy alone followed by bonding of orthodontic brackets. The patients will be recalled 6 and 12 months post-irradiation. Outcome measures will be visual examination with International Caries Detection and Assessment System criteria and SoproLife fluorescence. Data will be analyzed by Student’s *t* test for paired samples and proportional odds logistic regression model, *p*<0.05.

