### Eligibility

#### Inclusion criteria

Participants in the study are 12–18-year-old children, in good general health;Children, requiring fixed orthodontic treatment (fixed braces);Children at high caries risk according to “Oral disease risk assessment tool” accepted and used in the Department of Paediatric Dentistry, Faculty of Dental medicine, Medical University – Plovdiv, Bulgaria (see supplementary data file S1 “Appendix for risk assessment of oral diseases”);Children with untreated non-carious vestibular surfaces of the six maxillary anterior teeth of the permanent dentition (central and lateral incisors, canines) with ICDAS code 0 [22–24];Verbal assent from the child willing to comply with all study procedures and protocol; andObtained written informed consent by the patient’s parent/guardian for participation in the study (see supplementary data file S2 “Patient consent form” and S3 “Information leaflet”).

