#### Sample size calculation

The sample size calculation is based on our primary outcome endpoint of changes in ICDAS score on the vestibular surfaces of the anterior maxillary teeth in the left and the right quadrants per subject, by comparing the proportion of teeth with worsening ICDAS score in experimental in comparison to the control group. To determine the sample size for each group, a priori power analysis was conducted as follows:
$$ n=\frac{\left(z\frac{\upalpha}{2}+\mathrm{z}\upbeta \right)2\left(p1\left(1-p1\right)+p2\ \left(1-p2\ \right)\right)}{\begin{array}{c}\left(p1-p2\right)2\\ {}\end{array}} $$

*p*1: 8.7% of the lesion incidence in the control group

*p*2: 3.6% of the lesion incidence in the laser group

The data for this power analysis were obtained from a previous study.^9^ The significance level was considered as 95% and power was 80%. By inserting the minimum values in the above formula, the sample size was calculated as 241 teeth (121 teeth per group, i.e., a total number of 41 patients).

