## Statistical methods

The obtained data will be recorded, tabulated, processed, and analyzed using SPSS (Statistical Package for Social Science software) version 21.0 (IBM, USA). Descriptive statistics will be calculated. For the split-mouth randomized controlled trial Student t-test for paired samples will be used for the analysis. Mixed effects proportional odds regression modeling with outcomes of ICDAS and SOPROLIFE scores will be calculated. The inter-observer reliability and agreement will be estimated by Kappa coefficient where Kappa coefficient values above 0.80 are considered acceptable. Missing Completely at Random (MCAR) will be used to handle the missing data.

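### The protocol names two unranked primary outcomes but sizes a single endpoint, and does not say which outcome and test decide the trial

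*Protocol article*

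**What the plan says.** Four parts of the protocol article bear on this.

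- **Primary outcome measures:** "The primary outcome measures are the number of newly appeared caries lesions and the changes into ICDAS scores", experimental against control teeth within a patient, from baseline to 12 months. There is no ranking, and nothing says whether one or both must succeed.
- **Sample size calculation:** the calculation is "based on our primary outcome endpoint of changes in ICDAS score", in the singular, and proceeds "by comparing the proportion of teeth with worsening ICDAS score in experimental in comparison to the control group". The rates put in, 8.7% and 3.6%, are labelled lesion incidence.
- **Statistical methods:** "For the split-mouth randomized controlled trial Student t-test for paired samples will be used for the analysis", with no outcome attached; and "Mixed effects proportional odds regression modeling with outcomes of ICDAS and SOPROLIFE scores will be calculated". The Abstract puts both methods under one threshold: "samples and proportional odds logistic regression model, *p*<0.05".
- **Inclusion criteria:** the six maxillary anterior teeth must be sound at entry ("central and lateral incisors, canines) with ICDAS code 0").

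**The concern.** The outcome section fixes two primary outcomes and the sample size section fixes one. The sample size section also calls its endpoint a change in score while sizing it as an incidence. The t-test has no assigned outcome, and the model addresses ordered scores, so neither is stated to test the sized proportion.

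A reader of the final report could not tell which p-value the trial had committed to. A significant result on either outcome, by either method, could be presented as the primary finding. With few lesions expected, giving a handful of them code 2 instead of code 1 can be enough to move one analysis across 0.05 and not the other.

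**Working it through.** **1. The plan's own figure.** Inputs from the sample size section: p1 = 0.087, p2 = 0.036, two-sided 5%, power 80%.

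- p1(1−p1) + p2(1−p2) = 0.0794 + 0.0347 = 0.1141
- (p1−p2)² = 0.051² = 0.002601
- n = (1.96 + 0.84)² × 0.1141 / 0.002601 = about 344; 345 per group with unrounded z-values

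The protocol states 121 per group, so its figure is not reproduced. That is a separate defect and does not affect which endpoint is primary. The steps below use the stated 41 patients.

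**2. Expected lesions.** 41 patients × 3 teeth = 123 teeth per side. Control: 123 × 0.087 = 10.7. Laser: 123 × 0.036 = 4.4. Total: 15.1.

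**3. How many primary tests are open.**

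| | Lesion count | ICDAS change |
|---|---|---|
| Paired t-test (no outcome named) | open | open |
| Proportional odds model (ICDAS, SoproLife) | not stated | open |

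This makes three. The model on SoproLife concerns a secondary outcome.

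**4. Overlap of the outcomes.** Since all teeth start at ICDAS 0, a tooth worsens exactly when it gains a lesion. Only severity above code 1 separates the two measures, so their tests are strongly correlated. For two two-sided 5% tests, the chance that at least one is significant under the null is:

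| Correlation | Either significant |
|---|---|
| 0 | 1 − 0.95² = 9.75% |
| 0.8 | 7.8% |
| 0.9 | 7.0% |
| 0.95 | 6.5% |

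**5. Null simulations of this design** (41 patients, 3 teeth per side, t-test on both outcomes). Incidence, severity mix and clustering are assumptions; the protocol gives no severity mix or clustering.

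- *Pairing by patient, about 6% incidence, 40% of lesions at code 2.* Two sets of runs, over a range of clustering, gave either-significant rates of 5.0–6.1% and 5.4–6.3%. Single tests gave 4.0–4.8% and 4.2–5.1%. The second outcome adds about 1–2 points.
- *Pairing by patient, wider mix (50% code 1, 40% code 2, 10% code 3), incidence 8.7% to 40%.* Either-significant was 5.9–7.7%, with a correlation of 0.80–0.92 between the outcomes.
- *Tooth-level t-test, about 6% incidence, 40% code 2.* Either-significant was 5.7%, 8.4% and 10.1% with no, moderate and strong quadrant clustering. One test alone gave 4.2%, 6.3% and 8.2%. The differences are 1.5, 2.1 and 1.9 points.

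**6. How often the choice decides.** In the wider-mix runs at 8.7% incidence without clustering, the rates were 5.08% (count), 4.95% (score) and 6.775% (either). Exactly one outcome was significant in 2 × 6.775 − 5.08 − 4.95 = 3.5% of null trials. That is about half of the trials with any significant result (3.5 / 6.775 = 52%). So when a false positive occurs, the two outcomes often disagree.

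The added error from the model as a second method was not computed.

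**The case against.** **The endpoint is largely identified already.** The sample size section speaks of one endpoint, and with sound teeth at entry its proportion is the new-lesion outcome at tooth level. This stands in part. A reader might infer that the trial was sized on something unrelated to its primary outcomes; the documents do not support that, because the sizing covers one of the two. It still conflicts with the outcome section, which gives the score change equal standing.

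**Ranking and alpha sharing can be left to an analysis plan that is not shown.** This is fair as far as silence goes. But the disagreement on the number and form of the primary outcomes lies between two sections of the protocol itself, where the primary outcome should be fixed.

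**The statistician is masked to side.** Labelling the quadrants 0 and 1 guards against choosing by direction. It does not guard against choosing the outcome or test with the smaller p-value, which is visible without the key.

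**The inflation is small.** This stands. Two stronger readings are tempting and should not be made:

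- *Four tests, or an error near 1 − 0.95⁴ = 18.5%.* Statistical methods ties the model to the ICDAS and SoproLife scores and not to lesion count, and the tests are far from independent.
- *A false-positive rate of 8–10% from the two outcomes.* Those figures come mainly from a tooth-level t-test that ignores clustering, under which one test alone already reaches 6.3–8.2%. The protocol does not specify a tooth-level test and frames the comparison within one patient.

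**Conclusion.** The point holds as an internal conflict: two unranked primary outcomes in one section, one sized endpoint in another, and two methods of which neither, as written, directly compares the sized proportion. Up to three primary tests are open.

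The numerical inflation from the second outcome is modest: about 1–2 percentage points, or about 5–6% either-significant with pairing by patient, at about 6% incidence and 40% of lesions at code 2. These settings are assumed. A wider severity mix and higher incidence raised the rate to at most 7.7%. Any effect of the second method comes on top.

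The greater harm is the freedom to choose. With about 15 lesions expected, the outcome and test that decide the trial can be settled after the data are seen. The change should be made; it is a matter of wording and does not call the design into question.

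**What to change.** Reconcile the outcome, sample size and statistical sections as follows.

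1. **One primary endpoint, the one sized:** the proportion of vestibular surfaces with ICDAS 1 or more at 12 months.
2. **One primary test that respects the split-mouth pairing and the three teeth per side.** An example is a paired comparison of each patient's lesion proportion on the two sides. With three teeth scored per side this equals comparing lesion counts (proportion = count / 3), so the paired t-test already named can serve once it is assigned to this outcome with the patient as the unit. Single tests of this kind stayed at about 4–5% in the null simulations.
3. **Ordinal ICDAS change and the proportional odds model** become secondary or supportive.
4. **If both outcomes must stay primary,** test in fixed order at 5%: incidence first, then ICDAS change only if incidence is significant.

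The cost is wording in the protocol and the registry entry. Neither route needs more patients for multiplicity. An even alpha split would: with the protocol's own inputs and formula, 2.5% per outcome raises the requirement from 345 to 418 teeth per group (345 / 3 = 115 patients to 418 / 3, rounded up, = 140). The small downside is that the ordinal score alone can no longer carry the primary claim.

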#### Secondary outcome measures

The secondary outcome measures are changes in SoproLife® scores in the experimental and control teeth (within one patient) from baseline to 12 months. The SOPROlife score is a visual assessment of the caries levels. The SoproLife® daylight intraoral camera (SoproLife® Daylight mode) is used to record an intraoral picture with Sopro-imaging software (Acteon, Sopro, La Ciotat, France). The SoproLife® blue fluorescence mode scores range from 0 to 5. Code of “0” is given when the surface appears shiny green, the enamel appears sound, and there are no visible changes’ code “1” a tiny, thin red shimmer is observed, no red dots appeared; code “2” darker red spots are visible; code “3” dark red spots have extended, a slight beginning roughness of the red areas can be visible; and codes “4–6” represent larger carious lesions in dentin. Time frame: 1 year.

#### Participant’s timeline

Each eligible patient undergoes three visits. The first appointment includes screening, consenting and assenting, recording of initial values, topical fluoride application, and treatment with the selected specific parameters of CO_2_-laser of the left maxillary anterior teeth and Placebo procedure for the right, contralateral teeth, and orthodontic treatment at the end of the visit. The second appointment at the 6-month recall includes an oral examination, cleaning of the investigated surfaces, collection of data values, reapplication of the fluoride varnish. The third appointment at the 12-month recall includes an oral examination, cleaning of the investigated surfaces, collection of data values, reapplication of the fluoride varnish.

#### Sample size calculation

The sample size calculation is based on our primary outcome endpoint of changes in ICDAS score on the vestibular surfaces of the anterior maxillary teeth in the left and the right quadrants per subject, by comparing the proportion of teeth with worsening ICDAS score in experimental in comparison to the control group. To determine the sample size for each group, a priori power analysis was conducted as follows:
$$ n=\frac{\left(z\frac{\upalpha}{2}+\mathrm{z}\upbeta \right)2\left(p1\left(1-p1\right)+p2\ \left(1-p2\ \right)\right)}{\begin{array}{c}\left(p1-p2\right)2\\ {}\end{array}} $$

*p*1: 8.7% of the lesion incidence in the control group

*p*2: 3.6% of the lesion incidence in the laser group

The data for this power analysis were obtained from a previous study.^9^ The significance level was considered as 95% and power was 80%. By inserting the minimum values in the above formula, the sample size was calculated as 241 teeth (121 teeth per group, i.e., a total number of 41 patients).

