## Conclusion

This randomized control trial is a well-powered, one-center split-mouth experimental study. In split-mouth designs, experimental and control interventions are applied to different areas in the same oral cavity and the advantage is the reduction of the outcome variability estimation, leading to the potential increase in statistical power.

Fixed orthodontic treatment is associated with a high risk of initiation and development of caries lesions. CO_2_-laser has great potential in dental caries prevention. The study outlined in this protocol will be the first direct investigated combination of the preventive effect of the CO_2_-laser irradiation in addition to fluoride therapy and the fixed orthodontic treatment as a risk factor for dental caries. The implementation of CO_2_-laser in the regular protocol for the orthodontic treatment would significantly increase the success of this therapy resulting in lower rates of white spot lesions associated with it.

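### The sample size uses a formula for two independent groups of teeth although the trial compares sides within a patient; the stated 80% power at 41 patients is unsupported in either design

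*Protocol article*

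**What the plan says.** Protocol article, Sample size calculation: the calculation rests on "comparing the proportion of teeth with worsening ICDAS score in experimental in comparison to the control group". The inputs are "8.7% of the lesion incidence in the control group" and "3.6% of the lesion incidence in the laser group", with power 80% and a significance level given as 95%, read here as two-sided alpha 0.05 because the formula uses z at alpha/2. The variance in the printed formula is p1(1−p1) + p2(1−p2). The result is that "the sample size was calculated as 241 teeth (121 teeth per group, i.e., a total number of 41 patients").

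Inclusion criteria: each patient contributes the "six maxillary anterior teeth of the permanent dentition (central and lateral incisors, canines"), so three per side. Trial design and Participant's timeline place laser plus fluoride on one side and fluoride plus sham on the other side of the same mouth.

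Statistical methods: "For the split-mouth randomized controlled trial Student t-test for paired samples will be used for the analysis", and a mixed-effects proportional odds model is also planned.

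Conclusion: "This randomized control trial is a well-powered, one-center split-mouth experimental study". The next sentence there says that a split-mouth design can raise power by reducing variability. No correlation or discordance rate appears anywhere in the article.

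**The concern.** The printed variance is that of two separate groups in which every tooth is an independent unit. The step from 121 teeth to 41 patients is a division by three (121/3 = 40.3, rounded up). It treats three teeth in one quadrant as three independent observations, and the left and right sides of one mouth as unrelated.

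The planned comparison depends on two correlations that pull in opposite directions. Teeth on the same side resemble each other, which inflates the variance of a side's lesion proportion. The two sides of one mouth also resemble each other, which reduces the variance of their difference. The calculation contains neither, so it cannot yield the power of the analysis that will be run.

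The main risk lies in interpretation. If a trial described as well powered finds no difference, readers may take that as evidence that the laser adds nothing. There is a second risk: someone who notices the arithmetic error and merely re-evaluates the same formula would again print 80% for a different design.

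**Working it through.** **Inputs.** From the article: p1 = 0.087, p2 = 0.036, so d = 0.051; alpha 0.05 two-sided; power 0.80; three teeth per side; 41 patients, so 123 teeth per side. The article gives no rw or rb, so they are assumed and shown over a range.

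**Step 1. The plan's own figure.** The 2 after each bracket in the printed formula is read as a square.
- p1q1 = 0.087 × 0.913 = 0.0794
- p2q2 = 0.036 × 0.964 = 0.0347
- Sum = 0.1141
- n = (1.960 + 0.842)² × 0.1141 / 0.051² = 7.849 × 0.1141 / 0.002601 = 344.4, so 345 teeth per group, or 115 patients

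The stated 121 is not reproduced. Nor do common variants give it: pooled variance 348, continuity correction 386, arcsine 334, one-sided 5% 272, one-sided 10% 198. Leaving the z-sum unsquared gives 2.802 × 0.1141 / 0.002601 = 122.9, which is close to 121. That is only a possible source.

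**Step 2. Power of the formula's own design at the stated size.** With 123 independent teeth per side, SE = √(0.1141/123) = 0.0305 and d/SE = 1.674. Power = Φ(1.674 − 1.960) = 39%. With 121 teeth it is 38%.

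**Step 3. Variance of the planned comparison.** Take the left-right difference in the proportion of worsened teeth within each patient and average it over patients:

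Var = {[p1q1 + p2q2](1 + 2rw) − 6·rb·√(p1q1·p2q2)} / (3 × patients)

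Here √(0.0794 × 0.0347) = 0.0525. Divided by the Step 1 variance for the same number of teeth, this gives 1 + 2rw − 2.76rb (6 × 0.0525 / 0.1141 = 2.76). The unpaired formula is therefore conservative when rb exceeds about 0.72 × rw (2/2.76) and optimistic when rb is smaller.

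**Step 4. Power by normal approximation**, Φ(d/√Var − 1.960):

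| rw / rb (assumed) | Variance ratio | Power, 41 patients | Power, 115 patients | Patients for 80% |
|---|---|---|---|---|
| 0 / 0 | 1.00 | 39% | 80% | 115 |
| 0.2 / 0.2 | 0.85 | 44% | 86% | 98 |
| 0.3 / 0.2 | 1.05 | 37% | 78% | 121 |
| 0.3 / 0.1 | 1.32 | 31% | 68% | 153 |
| 0.3 / 0 | 1.60 | 26% | 60% | 184 |

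Example, 0.3/0.2 at 41 patients: numerator 0.1141 × 1.6 − 6 × 0.2 × 0.0525 = 0.1196; SE = √(0.1196/123) = 0.0312; d/SE = 1.635; power = Φ(−0.325) = 37%.

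The 41-patient column carries the arithmetic error of Step 1. The 115-patient column isolates the effect of using the wrong design. Loss to follow-up is not included.

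**Step 5. Can strong pairing rescue 41 patients?** At the stated rates, the correlation between a left and a right tooth cannot exceed √(p2q1/(p1q2)) = √(0.0329/0.0839) = 0.626. With rw = rb = 0.626, power at 41 patients is about 64%, but nothing in the article forces rw to equal rb. As an extreme pattern, let the control-minus-laser lesion count be 1 with probability 3 × 0.051 = 0.153 and otherwise 0. A patient-level paired t-test on 41 patients then rejects at four or more such patients (t = 2.08 against 2.02). The chance of four or more is 89%. So 80% is attainable, but only where almost no patient does worse on the laser side.

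**The case against.** The strongest reply is that the low power at 41 patients comes mainly from misevaluating the formula. That stands. With both correlations at zero, power is already 39%, and at 0.2/0.2 the split-mouth design raises it to 44%. At a correctly computed 115 patients the unpaired formula is even conservative when the two sides are about as alike as teeth within a side. The lowest figures need rb = 0, which is hard to believe for two sides of one mouth sharing diet, hygiene and saliva. What remains is that the direction cannot be known until correlations are stated.

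A reader might infer that no pairing benefit compatible with the stated rates could bring 41 patients to 80%. The documents do not support that: the 64% figure depends on setting rw equal to rb, and the extreme pattern in Step 5 reaches 89%. Tooth-level tests on 123 independent pairs likewise reach 82% to 88% at correlations of 0.60 to 0.626, though only 66% at 0.5, and an exact McNemar test never exceeds about 60%.

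A reader might also infer that 80% is right for independent teeth and merely belongs to another design. It is not right there either (38% to 39%). Nor does the Conclusion argue that pairing makes 41 patients enough; it speaks only of a possible gain.

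**Conclusion.** The point holds in this form. The sample-size formula does not match the planned within-patient comparison, and the stated 80% at 41 patients is unsupported in either design. Most of the gap is arithmetic: 345 teeth per group, not 121. The design mismatch is a separate defect of uncertain direction. After correcting the arithmetic, power at 115 patients runs from 60% to 86% over the four correlated cases tabulated. At 41 patients the same cases give 26% to 44%, and only extreme patterns reach 80%.

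These figures rest on the article's 8.7% and 3.6%, assumed correlations, the proportion of worsened teeth as endpoint, a normal approximation and complete follow-up. Power for the ordinal mixed model, or for a t-test on ICDAS scores, cannot be computed from the article.

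**What to change.** In Sample size calculation, replace the independent-proportions formula with the variance of the patient-level left-right difference given in Step 3. State the assumed rw and rb and their basis, and print either the resulting power at 41 patients as a range or the detectable difference. Withdraw the figure of 121 teeth as the requirement for 80% power. In Conclusion, remove the description of the trial as well powered, or qualify it with that range.

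The cost is one rewritten paragraph and one changed sentence. No extra patients or procedures are required, and 41 patients can stay if recruitment cannot change. The downside is a less favourable stated power.

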### Recruitment

The patients at the Department of Paediatric Dentistry of the Faculty of Dental Medicine, Medical University – Plovdiv, Bulgaria, who meet the inclusion criteria, will be screened for eligibility. Once identified, patients will be informed about this research project and will receive information about the possibility of potential study participation. Patient recruitment starts obtaining the full quota of participants within a 1-year time frame. It begins in September 2021 with an estimated enrollment capacity of 4 patients per month.

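### The stated 80% power makes no allowance for loss by month 12: the 41 patients are only 121 teeth per side divided by three and rounded up, and 121 is not what the printed formula gives

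*Protocol article*

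**What the plan says.** The sample size section of the protocol article sets out its whole calculation: a two-proportion formula, the two rates ("8.7% of the lesion incidence in the control group" and "3.6% of the lesion incidence in the laser group"), and the error levels ("The significance level was considered as 95% and power was 80"%). It concludes that "the sample size was calculated as 241 teeth (121 teeth per group, i.e., a total number of 41 patients"). The formula has no attrition term, and no dropout rate appears in the section or elsewhere in the article.

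The inclusion criteria define the study teeth as the "six maxillary anterior teeth of the permanent dentition (central and lateral incisors, canines"), which gives three per side. The primary outcome runs from baseline to 12 months, with recalls at 6 and 12 months. The statistical methods section says that missing data will be handled under a missing-completely-at-random assumption. The recruitment section allows one year and says of accrual: "It begins in September 2021 with an estimated enrollment capacity of 4 patients per month". It refers to a full quota but puts no number on it. The conclusion calls the trial well powered.

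**The concern.** A power statement for a 12-month outcome applies to the patients who can be assessed at 12 months. Here the calculated number is carried to patients by division and rounding alone, so the 80% applies only if every child returns. The participants are adolescents who must attend two recalls six months apart, and the plan itself provides for missing values. At stake is the power claim: readers will take 80% as describing the trial as it will be analysed, whereas on the plan's own terms it is the most that complete follow-up could give.

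**Working it through.** **Inputs.** p1 = 0.087, p2 = 0.036, two-sided alpha 0.05 (the formula uses z at alpha/2; the 95% is read as 1 − alpha), power 0.80, and 121 teeth per group, all from the sample size section. Three teeth per side per child come from the inclusion criteria. Loss rates are assumed, because none is given. Teeth are treated as independent, as in the printed formula.

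**1. From teeth to patients.** 121/3 = 40.3, rounded up to 41, which reproduces the stated figure. 41 × 3 = 123 teeth per side and 40 × 3 = 120. Rounding explains the patient number completely, so no attrition factor is hidden in it.

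**2. Loss, taking 121 teeth per side as giving 80%.** Power at n teeth per side = Φ[(1.96 + 0.8416) × √(n/121) − 1.96].

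| Patients lost | Teeth per side | Power |
|---|---|---|
| none | 123 | 80.6% |
| one child | 120 | 79.7% |
| 10% (assumed) | 110.7 | 76.4% |
| 20% (assumed) | 98.4 | 71.4% |

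Setting 80% at 123 teeth instead gives 75.7% and 70.7% in the last two rows. Either way the answer is about 76% and 71%.

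**3. Is 121 the right base?** Reading the 2s in the printed formula as exponents:

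- p1(1 − p1) + p2(1 − p2) = 0.079431 + 0.034704 = 0.114135
- (p1 − p2)² = 0.051² = 0.002601
- (1.96 + 0.8416)² = 7.849
- n = 7.849 × 0.114135 / 0.002601 = 344.4, so 345 teeth per group, or 345/3 = 115 patients before any loss

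The stated 121 does not reproduce. Leaving the z-sum unsquared gives 2.8016 × 0.114135 / 0.002601 = 122.9, close to 121 but not equal to it. A missed square is a possible source but is not established.

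**4. Loss, using the printed formula and rates.** Power = Φ[0.051 / √(0.114135/n) − 1.96].

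| Patients lost | Teeth per side | Power |
|---|---|---|
| none | 123 | 38.8% |
| 10% (assumed) | 110.7 | 35.5% |
| 20% (assumed) | 98.4 | 32.2% |

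**5. The accrual capacity.** 4 per month × 12 months = 48 patients, and 48 × 3 = 144 teeth per side. The formula in step 4 gives about 44% power at 144 with no loss at all.

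**The case against.** The strongest reply is that this is an omission in a condensed article, not an error: the division is right, and the section never says that 80% holds after losses. The division is indeed right. But the article prints the calculation from formula to patient total, and the total leaves no room for an allowance kept elsewhere. What can be criticised is the published number and the power attached to it.

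A second reply is that the effect is small. For one child that is correct. A reader might infer from 123 against 121 that a single lost child undermines the trial, since 120 is below the target. The documents do not support that: crossing a rounding threshold leaves power only about 0.3 points under 80%. The effect becomes material at losses of roughly 10% or more, and the plan gives no rate, so its size rests on assumed values.

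A third reply is that the article does not say enrolment stops at 41. That stands. The recruitment section leaves the quota unnumbered, and its capacity comes to 48. A reader might infer either that the quota is fixed at 41 or that 48 is a dropout buffer; the text says neither. Nor would 48 be a remedy, as step 5 shows.

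A reader might also take the discontinuation criteria ("The patient withdraws consentInter-current illness preventing further treatment") as a forecast of attrition. They concern stopping or modifying the intervention, and the laser or sham procedure is given once, at the first visit. The missing-data sentence is the firmer support.

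Finally, the fall from 80% to 71% starts from a power that the printed inputs do not deliver. This also stands, so the figures in step 4 must be given beside those in step 2. Within-mouth pairing does not rescue 121: a McNemar calculation with the stated rates needs about 152 to 351 tooth pairs, depending on the discordance assumed.

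**Conclusion.** The point holds in a limited form. The 41 patients contain no allowance for loss by month 12, so the stated 80% could apply only to complete follow-up. At assumed losses of 10% to 20%, a nominal 80% falls to about 76% to 71%. On the printed formula and rates the corresponding fall is from about 39% to about 36% to 32%.

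The wrong tooth count is the larger fault of the two, and an attrition allowance alone would not repair it. Correcting the count would not settle attrition either: 115 patients obtained by dividing 345 by three again assumes that no one is lost. All figures treat teeth as independent. Clustering and pairing within a child could move them, and the documents give no correlation from which to judge by how much.

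**What to change.** In the sample size section:

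1. Recompute the tooth count from the printed formula and rates (about 345 per group, not 121), or correct the formula or rates if they are misprinted.
2. State that the calculated number is the number evaluable at 12 months.
3. Replace the 80% with the power at the number of patients expected to be evaluable, under an explicit attrition assumption labelled as such, for example 10% and 20%. At 41 enrolled and the printed rates, that is about 36% and 32%, beside about 39% with no loss.
4. Do not present 121 teeth or 41 patients as an adequate evaluable minimum, and do not rely on 48 enrolled as the remedy.
5. Bring the conclusion's description of the trial as well powered into line with the restated figure.

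The cost is a recalculation, some rewording and a less favourable stated power.
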